# Multimodal brain imaging effect of “Adjust Zang-fu and Arouse Spirit” electroacupuncture on diabetic cognitive impairment: study protocol of a randomized, sham-controlled pilot trial

**DOI:** 10.1186/s13063-021-05842-0

**Published:** 2021-11-25

**Keywords:** Electropuncture, Diabetic Cognitive Impairment, Multimodal brain imaging; Randomized controlled trial, Study protocol

## Abstract

**Background:**

Diabetic cognitive impairment (DCI) is a serious chronic complication caused by diabetes. The pathogenesis of DCI is complex, but brain nerve injury and brain nerve cell apoptosis are important pathological changes. Multimodal brain imaging is one of the most important techniques to study the neural mechanism of the brain. For the clinical treatment of DCI, there is no effective targeted Western medicine and a lack of clear drug intervention methods. Therefore, there is an urgent need to find effective complementary and alternative methods and clarify their mechanism. This research seeks to explore the multimodal brain imaging effect of “Adjust Zang-fu and Arouse Spirit” electroacupuncture for DCI.

**Methods:**

This clinical research will be a randomized, sham-controlled pilot trial. Eligible participants will be randomly assigned to the intervention group (*n* = 60) and the control group (*n* = 30). The intervention group will be divided into the “Adjust Zang-fu and Arouse Spirit” electroacupuncture group (*n* = 30) and sham electroacupuncture group (*n* = 30). All participants will continue to receive routine hypoglycemic therapy. The treatment period is the same in both groups. The primary outcomes include functional magnetic resonance imaging (fMRI), magnetic resonance spectroscopy (MRS), Montreal Cognitive Assessment Scale (MoCA), and Clinical Dementia Rating (CDR). The secondary outcomes include blood glucose and blood lipid tests, Instrumental Activities of Daily Living Scale (IADL), Hachinski Ischemic Scale (HIS), Self-Rating Anxiety Scale (SAS), and Self-Rating Depression Scale (SDS). Outcomes will be assessed at baseline and before and after treatment, and adverse events will be examined. Inter- and intragroup analyses will be performed.

**Discussion:**

This randomized controlled study, combined with multimodal brain imaging techniques and a clinical evaluation scale, was designed to explore the mechanism of “Adjust Zang-fu and Arouse Spirit” electroacupuncture in improving the central nervous system in DCI.

**Trial registration:**

Chinese Clinical Trial Registration ChiCTR2000040268. Registered on 26 November 2020

## Background

Diabetes mellitus (DM) is a chronic disease that causes huge economic and social burdens. In recent years, a large number of studies have proven that DM has become an independent risk factor for cognitive impairment. The incidence of cognitive impairment is 1.5 times higher in type 2 diabetes mellitus (T2DM) patients than in non-DM patients [1], with 60 to 70% of T2DM patients having varying degrees of cognitive impairment [2]. Diabetic cognitive impairment (DCI) is a serious chronic complication caused by diabetes and is mainly manifested as deficiency of attention, visual structure, learning function, verbal memory, and calculation ability [3]. It is a state of cognitive impairment between brain aging and dementia that belongs to the early stage of Alzheimer's disease (AD) [4]. Serious cognitive deficits, especially in executive function, impact the self-care and medical compliance of these patients. DCI brings a serious burden to patients’ families and society, and thus effective prevention, early diagnosis, management, and treatment of DCI have become the focus of clinical research.

Studies have shown that patients with DCI have brain atrophy, neurofibril tangles, senile plaques, regional neuronal apoptosis, and other pathological changes [5, 6]. Although the pathogenesis of DCI is complex, brain nerve injury and brain nerve cell apoptosis are important pathological changes of DCI that result in brain functional area atrophy, functional connection network changes, and other pathological changes [7]. In recent years, the rapid development of multimodal brain imaging technology has provided new research ideas and techniques for scholars to carry out DCI research at the living human level. Several studies using functional magnetic resonance imaging (fMRI) have found that the brain function and structure of patients with DM show changes similar to those of dementia. For example, the volume and thickness of the hippocampus and other brain regions, such as the hippocampus, entorhinal cortex and medial temporal lobe, are atrophied and are closely related to emotion, speech, and memory [8–10]; the connectivity of the default mode network and control network is impaired [11]; the expression levels of N-acetylaspartate and γ-aminobutyric acid in the brain are decreased; and myo-inositol, glutamate and glycine are increased [12]. Therefore, the close combination of brain imaging with pathophysiology and clinical research will be an important means to uncover the mystery of DCI, AD and other diseases.

At present, the exact pathogenesis and effective treatment methods of DCI are in the exploratory stage. There is no specific Western medicine for the effective treatment of DCI, and there is a lack of clear drug intervention methods. Acupuncture is an important method for the prevention and treatment of DM and its complications, which can control blood glucose and regulate brain activation areas and abnormal brain functional connections. Studies have confirmed that acupuncture combined with metformin therapy can more effectively improve the level of fasting blood glucose in patients with T2DM [13]. Many studies have found that acupuncture can alter the changes in brain regions and functional connectivity related to cognition in patients with AD and MCI [14–16]. Therefore, in this proposed study, we aimed to (1) carry out a randomized, pseudocontrolled clinical trial comprehensively using multimodal brain imaging techniques to reveal the changes in brain structure and function in patients with DCI, (2) clarify the brain function network effect of “Adjust Zang-fu and Arouse Spirit” electroacupuncture to prevent and improve cognitive dysfunction in patients with DCI, and (3) analyze the correlation between the changes in clinical cognitive function and the changes in brain structure and function.

## Methods/design

### Study design

This is a randomized controlled trial. The protocol was approved by the Medical Ethics Committee of the Third Affiliated Hospital of Changchun University of Chinese Medicine (approval No. of ethics committee: CZDSFYLL2020-001-01) and registered at the Chinese Clinical Trial Registry (registration number: ChiCTR2000040268, protocol version number: V3.0, 02 October 2020.).

In this study, the tested patients will be randomly divided into two groups: an intervention group and a control group. Patients who meet the inclusion and exclusion criteria will first complete informed consent and then be randomized and stratified according to the clinical treatment. The intervention group will be divided into the “Adjust Zang-fu and Arouse Spirit” electroacupuncture group, which will be treated with electroacupuncture on a fixed prescription of acupoints, and the sham electroacupuncture group, which will be treated with electroacupuncture on nonacupuncture points and a sham instrument.

### Setting of the study

This clinical trial will be conducted at the third Affiliated Hospital of Changchun University of Chinese Medicine (Changchun, China). Eligible participants will be randomly assigned to the intervention group (*n* = 60) and the control group (*n* = 30). The intervention group will be divided into the “Adjust Zang-fu and Arouse Spirit” electroacupuncture group (*n* = 30) and sham electroacupuncture group (*n* = 30). The total observation period will include a − 3~0-day baseline selection period, an 8-week treatment period, and a 6-month follow-up period. They will receive 40 sessions of electroacupuncture or sham electroacupuncture treatment over 8 weeks (five sessions per week). Assessments will be conducted at baseline and at 4 and 8 weeks after randomization, as well as at 1, 2, 3, and 6 months after treatment. Figure 1 illustrates the study flowchart. This protocol will be reported according to the SPIRIT 2013 [17] statement of recommendations for intervention trials: Defining Standard Protocol Items for Clinical Trials. The trial process was designed according to the STRICTA 2015 [18] report (Table 1).

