### Inclusion criteria

Eligible participants for DCI subjects should meet the following inclusion criteria: (1) the 2020 American Diabetes Association Standards of Medical Practice for diabetes with a duration of ≥ 2 years; (2) signs or symptoms of memory loss; (3) Montreal Cognitive Assessment Scale (MoCA) score < 26 points, Clinical Dementia Rating (CDR) ≥ 0.5 points; (4) activities of daily living (ADLs) not significantly affected, and instrumental ability of daily living (IADL) score ≥ 16 points; (5) aged 50–70 years, with more than 6 years of education, able to complete a cognitive assessment; (6) sufficient visual and auditory discrimination to undergo neuropsychological testing; (7) no evidence of infection, infarction, or other focal injury, or associated clinical symptoms, as detected by transcranial CT or MRI in the 12 months prior to screening; allows for white matter lesions or cavitary infarcts in noncritical brain regions without affecting the subject’s cognitive function; and (8) signed informed consent, volunteered to participate in the study, and were able to cooperate with the physician in completing the clinical study. Eligible participants who meet the following inclusion criteria as healthy subjects: (1) conditions such as age and education that are comparable to other groups of subjects; (2) absence of significant neurological foci and absence of associated disorders that could cause cognitive impairment, as determined by cranial MRI; (3) no religious beliefs, no bad habits, such as tobacco, alcohol, coffee, and tea; (4) no job or life stress during the observation period; (5) in good health, free of cardiovascular and other organic diseases; (6) total MoCA score ≥ 26 points; and (7) signed informed consent, volunteered to participate in the study, and were able to cooperate with the physician in completing the clinical study.

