### Randomization, concealment of allocation, and blinding

Participants who meet the inclusion criteria will voluntarily sign an informed consent form and will be eligible for random assignment. They will be assigned randomly to the “Adjust Zang-fu and Arouse Spirit” electroacupuncture group or sham electroacupuncture group. The randomization sequence will be generated by a statistician not involved in the intervention or outcome evaluation using IBM® SPSS® Statistics version 24.0 (IBM Research Corporation, USA). The randomization numbers and group assignments will be sent immediately to the independent assessor by another research coordinator via an encrypted electronic file. As much as possible, evaluators will be prevented from communicating with the patients to avoid bias. This process will ensure that randomization concealment will be competent and unaffected by the participants or practitioners.

Due to the particularity of electroacupuncture therapy, double-blinding of the therapist and patient is not feasible. Before signing the informed consent form, patients will be told that they will receive electroacupuncture treatment. Participants will be unaware of their treatment assignment. The therapist will not be blinded but will not assess the effectiveness of the treatment. Outcome assessors, data managers and statisticians will be blinded to treatment allocation. Prior to the start of the trial, all researchers will be trained to ensure the successful implementation of the blinding procedure.

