### Statistical analysis

#### Clinical data analysis

Statistical analysis of the clinical outcomes will be performed using SPSS 24.0 statistical software. All statistical tests will be bilateral, and *p* < 0.05 will be considered statistically significant. For clinical information, data will be presented as the mean ± standard deviation. Student’s *t* test and the chi-square test will be used to compare group differences at baseline. A paired *t* test will be used to compare the clinical outcomes within the groups. Analysis of variance and the Wilcoxon rank-sum (if normality is violated) will be used to compare the clinical feature changes between groups. The clinical data, including MoCA, CDR, HbA1c, TC, TGs, HDL-C, and LDL-C, will be converted to domain z scores for correlational analysis with imaging data. Missing data for the primary outcome will be imputed using the multiple imputation method.

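### The protocol says participants are randomized to a 30-person control group, but its own randomization and eligibility sections contradict this, and the between-group analysis does not say which groups it compares

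*Protocol article*

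**What the plan says.** Three places describe randomization to a control group. The abstract and Setting of the study both put 60 people in an intervention group, later split into 30 electroacupuncture and 30 sham, and 30 in a control group: "Eligible participants will be randomly assigned to the intervention group", and so on. Study design says "the tested patients will be randomly divided into two groups: an intervention group and a control group". Sample size estimation counts 90 patients in three groups of 30. The abstract adds: "All participants will continue to receive routine hypoglycemic therapy".

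Other sections describe a different study. Randomization, concealment of allocation, and blinding says "They will be assigned randomly to the “Adjust Zang-fu and Arouse Spirit” electroacupuncture group or sham electroacupuncture group" and mentions no third arm. Blood glucose control, Electroacupuncture intervention and the two treatment-group sections cover only electroacupuncture and sham. Inclusion criteria has one list for patients with diabetic cognitive impairment (DCI), who need MoCA below 26, and a second that begins "Eligible participants who meet the following inclusion criteria as healthy subjects". The second list requires "total MoCA score ≥ 26 points", good health, and "conditions such as age and education that are comparable to other groups of subjects".

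Clinical data analysis states: "Analysis of variance and the Wilcoxon rank-sum (if normality is violated) will be used to compare the clinical feature changes between groups". Neuroimaging data analysis repeats that pair of methods for the spectroscopy metabolites. Neither section names the groups.

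**The concern.** The sections disagree on who is randomized. If the 30 controls are the healthy subjects, chance cannot have placed them there: the two MoCA criteria do not overlap, so group membership is fixed before any allocation. A comparison of patients with healthy people is then observational, whatever the allocation sentence says.

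The analysis inherits the ambiguity. MoCA and spectroscopy are both primary outcomes, and the test for each is a comparison between unnamed groups. The trial includes a sham arm to separate electroacupuncture from placebo. Only the electroacupuncture-versus-sham comparison does that. A test that also included healthy subjects could be significant merely because patients and healthy people change differently over time, for example through regression to the mean, practice, or a ceiling on the scale.

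**Working it through.** **Who is in the third group.** Side by side:

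| Section | Groups described |
|---|---|
| Abstract; Setting of the study | Randomized: intervention 60 (electroacupuncture 30, sham 30) and control 30 |
| Study design | Patients randomized to intervention or control |
| Randomization, concealment of allocation, and blinding | Randomized: electroacupuncture or sham only |
| Intervention sections | Electroacupuncture and sham only |
| Inclusion criteria | DCI patients (MoCA < 26); healthy subjects (MoCA ≥ 26) |
| Sample size estimation | Three groups, 90 patients |

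Three groups less electroacupuncture and sham leaves one. The only other population defined is the healthy list, which itself refers to the other groups of subjects. If the controls were instead DCI patients, the randomization section would omit a randomized arm, and the healthy subjects would be a fourth group absent from the sample size. One set of sections is wrong on either reading.

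**The plan's own figures.** 24 / (1 − 0.20) = 30 per group, and 3 × 30 = 90. Both reproduce. They confirm three groups but not who is in the third. The starting figure of 24 cannot be checked because no SD is given, and nothing here depends on it.

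**What a three-group test would do if healthy subjects entered it.** Assumptions, none of them in the protocol: electroacupuncture exactly equals sham; both patient arms change by d = 1.0 or 1.5 MoCA points; healthy subjects do not change; the SD of change is 2 or 3. From the protocol: n = 24 (after dropout) or 30 per group, and a significance level of 0.05.

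The means are (d, d, 0), with grand mean 2d/3. The sum of squared deviations is 2(d/3)² + (2d/3)² = 2d²/3. The noncentrality is λ = n × (2d²/3) / SD², with 2 and 3n − 3 degrees of freedom (69 or 87). For d = 1.5, SD = 2, n = 24: λ = 24 × 1.5 / 4 = 9.0, and the probability of a significant F test is 75%.

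| d | SD | λ, n = 24 | P(significant) | λ, n = 30 | P(significant) |
|---|---|---|---|---|---|
| 1.0 | 3 | 1.78 | 20% | 2.22 | 24% |
| 1.0 | 2 | 4.0 | 40% | 5.0 | 49% |
| 1.5 | 3 | 4.0 | 40% | 5.0 | 49% |
| 1.5 | 2 | 9.0 | 75% | 11.25 | 85% |

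**Could such a difference arise without any treatment effect?** A simulation (4000 runs per scenario) selected patients below 26 and healthy subjects at or above 26 on a baseline score with measurement error, with no effect of anything. Assumed: true-score SD 2.5, measurement SD 1.5 to 2, population means from 22 and 27 to 25 and 25. Regression to the mean alone gave a patient-minus-healthy difference in change of about 0.6 to 1.5 points. The three-group test was significant in 16% to 61% of trials (n = 24) or 19% to 72% (n = 30). The direct electroacupuncture-versus-sham t test was significant in 4.6% to 5.4%.

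**The case against.** No sentence equates the control group with the healthy subjects, and the flow diagram is not in the text available. The references to patients in Study design and Sample size estimation, and the abstract's statement that all participants continue hypoglycemic therapy, point towards DCI controls. This stands: the identification is an inference. It does not remove the contradiction.

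A reader might also infer that the plan specifies a three-group analysis of variance. It does not. The baseline Student's t test and the rank-sum fallback are two-sample methods, Electroacupuncture intervention says there are two groups, and the sample size rests on a two-group comparison. A two-arm analysis may be what was meant, and the problem with the test would then disappear.

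Nor is it established that healthy subjects are reassessed. Setting of the study describes the schedule alongside the 40 sessions of real or sham treatment, and the assessment timetable is not shown. The healthy criteria mention an observation period, but no repeat MoCA is stated. Without one, healthy subjects have no change score.

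Finally, contrasts and post hoc tests are often left to an analysis plan, so the absence of a post hoc procedure is not a fault here. The objection leaves intact the conflict over allocation and the need to say which groups are compared.

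**Conclusion.** The contradiction over who is randomized is certain and must be resolved. On the likeliest reading, the third group is healthy subjects, and the stated randomization to control is impossible.

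The consequence for the analysis is conditional. It requires that healthy subjects are followed up and that they enter a three-group test of change. Given both, and the assumed drift and SDs, a significant result would occur in about 20% to 85% of trials with electroacupuncture equal to sham.

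It is tempting to read this range as an inflated type I error, to be set against 5%. That is not supported: when patients and healthy people truly change differently, the omnibus null is false and rejecting it is correct. The error would lie in taking that rejection as evidence for electroacupuncture over sham. Nor does the protocol say that such a result would be reported as a randomized treatment effect. It only leaves room for that by not naming the comparison.

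**What to change.** 1. In the abstract, Study design, Setting of the study and Sample size estimation, say that 60 DCI patients are randomized 1:1 to electroacupuncture or sham, and that 30 healthy subjects form a non-randomized reference group. If the controls are in fact DCI patients, correct Inclusion criteria and the randomization section instead.
2. In Clinical data analysis and Neuroimaging data analysis, state that the treatment effect is the two-arm electroacupuncture-minus-sham comparison among randomized patients.
3. Label any patient-versus-healthy comparison as observational and report it separately.
4. Reconcile the abstract's sentence on hypoglycemic therapy for all participants with Blood glucose control, which mentions only the electroacupuncture and sham groups.

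The cost is wording in the protocol, and in the registry entry if it carries the same text. No new data or participants are needed.

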**Fig. 1 Fig1:**
[figure not shown]
Flow diagram of the study design

**Table 1 Tab1:** Acupuncture treatment details based on the STRICTA 2015 checklist

Item	Item number	Detail
**1.Acupuncture rationale**	1a) Style of acupuncture	Traditional Chinese Medicine
	1b) Reasoning for treatment	The treatment protocol was based on traditional acupuncture theory, previous studies guidelines, and the consensus of acupuncturists from the third Affiliated Hospital of Changchun University of Chinese Medicine
	1c) Extent to which treatment was varied	All participants will receive standardized treatment.
**2. Details of needling**	2a) Number of needle insertions per subject per session	16
	2b) Names of points used	Nine fixed points: GV20, GV24, BL13, BL20, BL23, ST36, SP6, LI4, LR3
	2c) Depth of insertion, based on a specified unit of measurement	From 0.5 to 1.5 cun
	2d) Response sought (e.g., *de qi* or muscle twitch response)	*De qi* sensation
	2e) Needle stimulation (e.g., manual, electrical)	Electrical stimulation: the electric stimulators (SDZ-V electroacupuncture apparatus, Suzhou Medical Appliance Factory, China) will be attached to needles at the GV20-GV24, unilateral BL13-BL23 and SP6-LR3 points, and a continuous wave of 2 Hz/100 Hz frequency, and an intensity of 0.1–1.0 mA will be applied
	2f) Needle retention time	30 min
	2g) Needle type	Sterile disposable stainless steel needles of various lengths and diameters (Hwato Brand, Suzhou Medical Appliance Factory, China; 0.3 mm × 25 mm/0.3 mm × 40 mm)
**3. Treatment regimen**	3a) Number of treatment sessions	40 treatment sessions in both acupuncture and sham acupuncture groups
	3b) Frequency and duration of treatment sessions	Five times a week, followed by a 2-day rest interval, for 8 successive weeks
**4. Other components of treatment**	4a) Details of other interventions administered to the acupuncture group (e.g., moxibustion, cupping, herbs, exercises, lifestyle advice)	No other interventions during the study period were allowed. Light diet and do not eat beef, lamb, seafood, mushrooms, and so on
	4b) Setting and context of treatment, including instructions to practitioners and information and explanations to patients	The study will be conducted at the acupuncture and massage center of the third Affiliated Hospital of Changchun University of Chinese Medicine. All patients will be admitted to the acupuncture therapeutic room for treatment. All information except patient allocated group will be provided to participants
**5.Practitioner background**	5) Description of participating acupuncturists	Acupuncturists who are registered Chinese Medicine Practitioners in China and have at least 3 years’ clinical experience in acupuncture practice. Besides, they went through training classes before this trial and simulation to ensure that they are able to provide identical acupuncture treatment in accordance with a pre-defined protocol
**6. Control interventions**	6a) Rationale for the control or comparator in the context of the research question, with sources that justify this choice	Based on traditional acupuncture theory, previous studies, and the consensus of acupuncturists from the third Affiliated Hospital of Changchun University of Chinese Medicine
	6b) Precise description of the control or comparator. If sham acupuncture or any other type of acupuncture-like control is used, provide details as for Items 1 to 3 above	For the Sham-electroacupuncture group: participants will receive superficial non-acupoint sham- electroacupuncture 40 sessions over 8 weeks. Non-acupoints will be needled through adhesive pads to the skin (for the fixation of needles) without penetrating the skin using 1 cun blunt needles. The needle parameters and treatment regimen are the same as for the electroacupuncture group. When turned on, electric acupuncture apparatus looks normal but has no current output

*Abbreviation*: STRICTA, Standards for Reporting Interventions in Clinical Trials of Acupuncture

